## Methods

### Study design

This is a randomized wait-list control trial that will evaluate the effectiveness, feasibility and acceptability of online CRAFT with a parallel group. Participants will be randomised to receive either online CRAFT for 6 sessions over 6 to 10 weeks or to a wait-list control group who are provided with CRAFT related reading materials during the waiting period. Outcomes will be assessed at baseline and then at 6- and 15-weeks post baseline. Outcome measures will be completed online independently of researchers or clinicians. The trial reporting will comply with CONSORT guidelines. Figure 1 provides an overview of the trial recruitment and process.

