### Randomisation and blinding

The randomisation procedure for this project will be conducted by an independent researcher ([name]) using STATA software (Version 18 MP) and with the 'randomizr' package. This researcher will not be involved in other aspects of project implementation, such as CRAFT delivery or data collection. The researcher (NS) who recruits the participants will have no access to the order of allocation. All participants will be allocated an identification number and, before completing their baseline measures, will be randomly allocated to either the CRAFT group or the wait list control group. Individuals randomized to the control group will be assigned a 6-week wait time.

All assessments are conducted online, thus minimizing the possibility of researcher bias. Analysis of results will be blinded to the clinicians delivering CRAFT. The clinicians will be provided with contact information of consenting participants and they will deliver the program as scheduled without knowing which group the person is allocated to. Trial participants will be informed their start date for the intervention as 1. as soon as possible (Group A—within 7 days) or 2. within 6 weeks (Group B—WLC) without being informed which group they are in. The need for unblinding is not anticipated.

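### Participants are described as unaware of their group, but the start date they are given is what separates the arms, and they rate every wellbeing outcome themselves

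*Protocol article*

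**What the plan says.** All locations are in the protocol article.

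- **Randomisation and blinding, participants.** Participants are told their start as "as soon as possible (Group A—within 7 days) or 2. within 6 weeks (Group B—WLC) without being informed which group they are in". The section closes by saying that unblinding is not expected to be needed.
- **Randomisation and blinding, control arm.** "Individuals randomized to the control group will be assigned a 6-week wait time".
- **Randomisation and blinding, clinicians.** They receive participants' contact details and "they will deliver the program as scheduled without knowing which group the person is allocated to".
- **Study design.** The comparator is a "wait-list control group who are provided with CRAFT related reading materials during the waiting period". Participants fill in the outcome measures online, without researchers or clinicians.
- **Measures.** DASS-21, SWLS, the Flourishing Scale and Brief-COPE are each described as self-report and are scheduled at baseline, 6 and 15 weeks.
- **Recruitment and follow-up procedures.** The order is telephone screen, verbal consent, randomisation and booking of the first appointment, then the link to written consent and the measures. Randomisation and blinding agrees that allocation comes before the baseline measures.

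**The concern.** The section presents participants as not knowing their group, yet in the same sentence gives them the information that identifies it. What is withheld is a label. What is disclosed is whether counselling starts now or after a wait.

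This matters because participants are also the outcome assessors. The primary domain is their own wellbeing, and the recruitment advertisements tell them that the program aims to improve their mental health. A week-6 difference in self-rated distress or life satisfaction can therefore combine the effect of CRAFT with the expectation of benefit in one arm and disappointment at waiting in the other. A reader who takes the section at face value would rate the risk of bias lower than the design warrants. If the start date is known when baseline is completed, the baseline scores may be affected too.

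**Working it through.** The main check is a comparison of statements. The plan has no figure on this point to reproduce.

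**1. Does the start date identify the arm?** Group A starts within a week. Group B is the wait-list control, and the same section assigns control a six-week wait. Read alone, a start within six weeks could include an early one, but the assigned wait rules that out. The start date therefore maps onto the arm.

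**2. What does a participant know at week 6?** The CRAFT arm is offered 6 sessions over 6 to 10 weeks, so by week 6 counselling has been on offer for most of the interval. The control arm has waited, with reading material. Each participant knows which of these happened, whatever label is withheld.

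**3. Who rates the outcomes?** The participant, on all four scales and at all three time points. The person who knows the condition is the person who scores it.

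**4. Is baseline protected?** The documented order is randomisation, then appointment booking, then the survey link. Nothing in that order keeps the start date from the participant until baseline is submitted. The article does not say exactly when the start date is communicated, so baseline scores *may* be given with it known.

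**5. Clinicians.** They deliver to the schedule. The interval since enrolment, or a client who mentions the wait or the reading, could reveal the arm. The article does not say when contact details reach them or whether they see the randomisation date. They do not rate the scales.

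**6. Illustration of sensitivity.** Inputs from Sample size calculation: 260 recruited and 20% attrition, so 260 × 0.80 = 208, or 104 per arm. Assumptions: a continuous outcome in SD units, a two-sided 5% test, no true effect, no covariate adjustment, and a differential reporting shift *b* that the documents do not give.

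- SE = √(2/104) = 0.139 SD
- P(reject) = 1 − Φ(1.96 − b/SE) + Φ(−1.96 − b/SE)

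| Assumed shift b | P(reject), 104 per arm |
|---|---|
| 0 | 5.0% |
| 0.1 SD | 11.1% |
| 0.2 SD | 30.3% |
| 0.3 SD | 58.1% |

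With the 108 per arm that the plan states before attrition, SE = √(2/108) = 0.136 and the last three rows become 11.4%, 31.2% and 59.7%.

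**The case against.** Participants in a wait-list trial of counselling cannot be masked to what they receive, and nowhere does the article call the trial blinded or double-blind. On this view the sentence means only that the label is withheld, which might leave a participant unaware that a later start is the comparison condition. The first part stands: lack of masking is inherent in the design and is not itself the fault. The second depends on study information that is not shown. Even if it were right, it would conceal the purpose of the wait, not the wait itself. The text also sits under a blinding heading and closes by discounting any need to unblind, which presupposes something to unblind.

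Several stronger readings are tempting but go beyond the documents:

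- *Clinicians certainly know the arm.* This is likely but not stated.
- *All the masking is illusory.* The recruiter has no access to the allocation order and an independent researcher randomises. Nothing here undermines that.
- *The article claims online surveys remove bias generally.* The sentence "All assessments are conducted online, thus minimizing the possibility of researcher bias" claims no more than it says about researchers.
- *Only the control arm gets reading material.* That is implied. The article does not say the CRAFT arm gets none.
- *No analyst is masked.* The article says "Analysis of results will be blinded to the clinicians delivering CRAFT", and further arrangements may be in documents not shown.

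It is also fair that the error rates in the table would apply to any unmasked trial with self-reported outcomes, and that rewording the section would not change them.

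**Conclusion.** The point holds for participants. They are told a start date that defines their arm, they know by week 6 whether they were offered counselling or waited, and they rate every wellbeing outcome. The participant masking that the section implies is a property the design does not have. Baseline self-reports may be exposed in the same way, given the order of enrolment steps. For clinicians the most that can be said is that masking cannot be assured.

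The documents do not allow the size of the bias to be estimated. A reader might infer from the table that this trial's false-positive rate is 30% or more. That is not supported: the figures show only how sensitive a comparison of this size is to an assumed shift of 0.1 to 0.3 SD. The finding rests on the stated procedures and not on those figures. The design can stand, but its description should be corrected.

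**What to change.** 1. In Randomisation and blinding, state that participants are not masked, that clinician masking cannot be assured, and that the wellbeing outcomes are participant-reported and open-label. Keep the statement on concealment from the recruiter.
2. Remove the words "without being informed which group they are in" and the closing sentence on unblinding, and replace the clinician wording in line with item 1.
3. Have the baseline survey submitted before the start date is disclosed. According to Trial duration the study began in October 2023, so record the date of this change so that participants enrolled before and after it can be distinguished.
4. When reporting, acknowledge that the week-6 contrast includes expectancy effects.

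**Cost.** Items 1, 2 and 4 are wording, at the price of a less favourable description of the design. Item 3 moves one step in enrolment and creates two baseline procedures within one trial, which is why the date must be logged. It protects baseline only and cannot mask the week-6 ratings.

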### Objectives of the study

This trial will determine the effectiveness of an online delivered CRAFT counselling intervention for improving the well-being of family members with a loved one experiencing substance problems with and without co-occurring mental health problems. It is hypothesised that CRAFT implemented online by accredited therapists will be more beneficial than CRAFT self-help information provided to the wait-list group. Compared to the wait-list control group, the CRAFT group will show significant decrease in self-reported levels of depression, anxiety and stress and significant increase in life satisfaction and that these improvements will be maintained over a three-month period post intervention.

It is hypothesized that 1) improvements in depression, anxiety and stress scores as a function of CRAFT relative to the control group will be mediated by: a) acceptability of receiving support online and b) ease of access. Given the lack of information regarding implementation parameters of substance use interventions for families of people with a mental health condition, qualitative methods will explore the experiences of study participants as well as clinicians delivering the program. The study has the following specific aims:

Aim 1: determine the effectiveness of an online delivered CRAFT counselling intervention on on self-reported levels of depression, anxiety, stress and life satisfactionAim 2: qualitatively examine the paricipants’ experiences about the acceptability of receiving support onlineAim 3: qualitatively examine the clinicians’ experiences of delivering the program and feasibility

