### Recruitment and follow-up procedures

Participants will be recruited from any rural areas in Australia by advertisements through healthcare and substance treatment agencies and health advice internet sites, in local newspapers and radio stations and paid geo-located (rural) social media advertisements (see Supplementary Material). The advertisement will include information about CRAFT, highlighting that the program’s goals are to improve the participants’ mental health and increase the likelihood of their relative’s engagement in treatment. Individuals who are interested in participating will register on a secure website or by contacting the study coordinator.

Those who are registered will be contacted within 48 h and invited to complete a short telephone screen using the inclusion and exclusion criteria. If eligible, the study information and process will be described, and verbal consent will be gained. Following this, participants are randomised to either the waitlist or intervention group, and a first initial appointment is organised with an in-community CRAFT practitioner. Participants will then be sent a link to the written consent form and outcome measures.

On average, the information and screening process will take approximately 20–30 min to complete. Once the consent is signed, the participant can access the online baseline measures for completion. If the measures are not completed, SMS reminders will be sent after 2 days. If the participant still does not complete the measures, they will be contacted by phone to confirm their intent to join the study and to ensure that they can access the survey. Participants who complete all three surveys (baseline, 6 and 15 weeks) will receive $120AUD in gift card for their time and participation. Individuals who have not responded to the initial call or have not completed the follow-up measures will be contacted on a weekly basis by both phone and SMS for up to 4 weeks after the follow-up is due.

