### Measures

The outcome measures will take participants approximately 20 min to complete (Table 1).

**Table 1 Tab1:** Baseline (BL) and follow-up measures assessment schedule

Instrument	Domain	BL	6 weeks	15 weeks
DASS 21	Psychological wellbeing	x	x	x
Satisfaction with Life Scale (SWLS)	Quality of life	x	x	x
The Flourishing Scale (FS)	Psychological wellbeing	x	x	x
Brief-COPE	Stress and distress management	x	x	x
Use of online delivery methods (session summary sheet)	Delivery experience		x	
Number and length of sessions attended Sessions delivered (Session summary sheet)	Feasibility Fidelity		x	
Experience interviews	Acceptability			x

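### Week 6 is the only follow-up at which controls can still be without CRAFT sessions, yet the start rule and the 4-week survey chase let them answer after session 1

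*Protocol article*

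**What the plan says.** All references are to the protocol article.

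- **Comparison of interest** (Objectives of the study): the hypothesis is that "CRAFT implemented online by accredited therapists will be more beneficial than CRAFT self-help information provided to the wait-list group".
- **Control start** (Randomisation and blinding): "Individuals randomized to the control group will be assigned a 6-week wait time". The next paragraph says participants in that arm are told they will start "within 6 weeks (Group B—WLC) without being informed which group they are in". The CRAFT arm is told it starts within 7 days.
- **Follow-up times** (Study design): "Outcomes will be assessed at baseline and then at 6- and 15-weeks post baseline".
- **Length of treatment** (Study design): participants "receive either online CRAFT for 6 sessions over 6 to 10 weeks", or go on the wait-list with reading material.
- **Late surveys** (Recruitment and follow-up procedures): people with an outstanding follow-up survey "will be contacted on a weekly basis by both phone and SMS for up to 4 weeks after the follow-up is due".
- **Order of events** (same section): after randomisation "a first initial appointment is organised with an in-community CRAFT practitioner". The consent link and the baseline measures come afterwards.
- **Exposure data** (Measures, Table 1): "Number and length of sessions attended" is scheduled at 6 weeks.

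**The concern.** The hypothesis needs a time at which the CRAFT arm has had sessions and the control arm has had only reading material. By week 15 most or all of the control arm's programme can have been delivered, so that time can only be week 6.

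The stated rules do not keep controls free of CRAFT when they answer the week-6 survey, for two reasons:

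1. A start at any time up to 6 weeks has an upper limit but no lower one. Read literally, it allows sessions before week 6.
2. Even if every control waits the full 6 weeks, the wait ends about when the survey falls due. The chase then runs through the first four weeks of the controls' treatment.

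A control who answers after session 1 no longer reflects self-help alone. Such answers would usually shrink the week-6 difference between arms.

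**Working it through.** The plan gives no figure for this overlap, so there is none to reproduce. The check is schedule arithmetic.

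**Inputs from the article**
- Six sessions over D weeks, with D from 6 to 10 (Study design); D = 6, 8 and 10 are used.
- Surveys at weeks 6 and 15 after baseline (Study design).
- Chase of up to 4 weeks (Recruitment and follow-up procedures), so the week-6 survey can arrive until week 6 + 4 = 10.
- CRAFT start within 7 days; control wait of 6 weeks (Randomisation and blinding).

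**Assumptions**
- Sessions accrue at an average rate.
- Weeks are counted from baseline.
- The CRAFT arm starts at week 0 or 1. Controls start at week 6, or at week 7 if they have the same lag of up to 7 days.

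**Formula.** Sessions received by week t = min(6, (t − start) × 6/D).

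**Step 1: control exposure**

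| Control start | Week t | D = 6 | D = 8 | D = 10 |
|---|---|---|---|---|
| 6 | 7 | 1.0 | 0.75 | 0.6 |
| 6 | 8 | 2.0 | 1.5 | 1.2 |
| 6 | 9 | 3.0 | 2.25 | 1.8 |
| 6 | 10 | 4.0 | 3.0 | 2.4 |
| 6 | 15 | 6 | 6 | 5.4 |
| 7 | 10 | 3.0 | 2.25 | 1.8 |
| 7 | 15 | 6 | 6 | 4.8 |

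Example: start 6, t = 10, D = 10 gives (10 − 6) × 0.6 = 2.4. By week 15 the range is 4.8 to 6 of 6 sessions, so week 15 is not a comparison with self-help.

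If a session is instead counted on the start day and sessions are weekly, a control starting at week 6 has had 1 by week 6 and up to 5 by week 10. The average-rate figures are the more cautious.

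**Step 2: session gap between arms (CRAFT minus control) if both arms answer at week 10 instead of week 6**

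| Starts (CRAFT/control) | D = 6 | D = 8 | D = 10 |
|---|---|---|---|
| 0/6 | 6 → 2 (−67%) | 4.5 → 3 (−33%) | 3.6 → 3.6 (0%) |
| 1/6 | 5 → 2 (−60%) | 3.75 → 3 (−20%) | 3.0 → 3.0 (0%) |
| 0/7 | 6 → 3 (−50%) | 4.5 → 3.75 (−17%) | 3.6 → 4.2 (+17%) |
| 1/7 | 5 → 3 (−40%) | 3.75 → 3.75 (0%) | 3.0 → 3.6 (+20%) |

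Example: starts 0/6, D = 8. At week 6 the gap is 4.5 − 0 = 4.5. At week 10 it is min(6, 7.5) − 3 = 3, and 3/4.5 − 1 = −33%. These figures describe late responders at the end of the chase, not the whole trial.

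**Step 3: illustration of dilution.** Suppose a share c of controls answers after starting and has gained a fraction f of the full effect, with no offset in the CRAFT arm. The contrast retained is 1 − c × f. Take a standardised difference of √(2/108) × (1.960 + 0.842) = 0.381, which gives 80% two-sided power at the plan's 108 per arm.

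| c | f | Contrast retained | Power |
|---|---|---|---|
| 10% | 1/6 | 98% | 79% |
| 20% | 1/3 | 93% | 74% |
| 30% | 2/3 | 80% | 61% |

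The values of c and f are assumptions; the article gives neither.

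**Step 4: order of events.** Randomisation and booking precede the baseline measures, and the surveys are timed from baseline. The article does not say when the wait begins. If it runs from randomisation, it ends at or before week 6 after baseline, and any delay in completing baseline moves session 1 further ahead of the survey.

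**The case against.** The strongest reply is that the start wording is only what participants are told while they are kept unaware of their group, and that the operative rule is the assigned 6-week wait. On that reading nobody starts early. This is plausible and would remove the first route. It leaves the second, because the survey still falls due as the wait ends and is still chased for four weeks.

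A second reply is that chasing late surveys is ordinary retention practice, and that the order of survey and session 1, the date fields and the handling of late responses belong in the full protocol or the analysis plan, neither of which is shown. This stands for date recording and for the sensitivity analysis, whose absence from the article is not a fault. It does not answer the timing point, since following the article's rules exactly still produces the overlap.

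A third reply is that no net harm is shown. The share of late controls is unknown, the gap change runs from −67% to +20%, and the mildest illustration loses almost nothing. This also stands as a limit on size: late CRAFT-arm responders have had more sessions too, which can cancel or reverse the dilution at slower paces. It is no reason to leave the only usable comparison open to avoidable contamination.

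Finally, the session sheets and the week-6 session count already give partial means of detecting exposure. That is true, but the article does not say that session dates are recorded.

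**Conclusion.** The concern holds. The rules as written allow controls to have CRAFT sessions before they answer the only survey that can compare CRAFT with self-help material. On a full 6-week wait, a control answering at the end of the chase would have had about 2.4 to 4 of 6 sessions (1.8 to 3 if started at week 7), assuming an average session rate and weeks counted from baseline.

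The effect on the trial result cannot be computed from the article. The usual direction is towards no difference, and the offset from late CRAFT-arm responses makes the net sign uncertain at slower session paces. The overlap itself is certain, its consequence is not, and confidence is medium. The protocol should be changed because the correction is cheap, not because a given loss has been shown.

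**What to change.** 1. **Control start.** Replace the open-ended start with a rule that the control's first session is booked no earlier than 6 weeks after baseline. Keep the surveys timed from baseline. Because booking comes before baseline, confirm the control's date once the baseline measures are in.
2. **Survey timing.** Open the week-6 survey in both arms a few days before week 6, and send both arms the same prompt to answer by week 6. For controls that is before session 1. Do not withhold treatment if the survey is late, and keep the 4-week chase.
3. **Dates.** Record the date of each survey and of each first session, if the full protocol does not already require it.
4. **Analysis.** Keep all responses in the primary intention-to-treat analysis. Add one sensitivity analysis that sets to missing any week-6 response after a calendar cut-off common to both arms, for example 6 weeks after baseline. A common cut-off avoids excluding controls according to their own session 1.

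Items 1 and 2 do most of the work and are worthwhile even if 3 and 4 are left to the analysis plan.

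**Cost.** One sentence, a change to survey-link timing, two dates and one extra analysis. Some responses will come a few days early, so the CRAFT arm is measured after slightly less treatment. A late baseline slightly delays some control starts. The prompt reduces late control responses but does not remove them. The sensitivity analysis discards late responses in both arms, which with the example cut-off means every response obtained by chasing, and it assumes they are missing at random. Recruitment began in October 2023, so the scheduling change covers only people enrolled after it.
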